### Recruitment

Patients with LARS and meeting the inclusion criteria will be offered participation in this clinical trial upon consultation with an abdominal surgeon or surgeon at the National Cancer Institute clinic (or any other participating center). The patient will be given time to think as much as necessary. All questions related to the clinical trial will be answered. The patient's decision to participate in the study or not will not have any effect on their further treatment and/or surveillance. Patients who have consented and signed the personal information form and the consent form will be included in the study. Only centers with a high volume of documented colorectal surgery can be included (centers performing at least 50 low anterior resections following neoadjuvant chemoradiotherapy per year may be assessed as candidates for participation).

### Informed consent

After patients are invited to participate in the study, they will be provided with information about this study. The research doctor or the person conducting the research authorized by the researcher provides information about the study to the subject. The doctor-researcher or the person conducting the research authorized by the researcher explains the information related to the research and the objectives of the research. If patients agree to participate in the study, they sign the informed consent form, indicating their name, surname, date, and time. The investigator will sign and date the consent form. The informed consent form is signed in two copies, one is given to the patient participating in the study and the other is kept at the study center (National Cancer Institute), in a secure place, with limited access to only the personnel of this biomedical study. The principal investigator is responsible for the storage of research documents.

### Randomization

Individuals participating in this study will be randomly divided into groups A and B by randomization (computer-generated random numbers and sealed envelopes will be used). The probability of falling into one or the other group is equal.
•Group A. This is a group of patients who will be subjected to transanal irrigation (experimental).•Group B. This is a group of patients who will receive only the best currently in use maintenance treatment (control).During the research, the name and surname of the subject will be replaced by a special code, restricting the identity of the subject. This code will be used in all study documents except the consent form. Only the main researcher and his representatives will have access to these data, and the staff performing the statistical analysis will not know which group the subject belongs to. Only the data analysts will be blinded to the patients groups (will get only data with names of Groups A and B, without any notification, of which group is which).

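### As written, the analysts' blinding can be decoded from the protocol: the labels in their data file are the same Group A and Group B that the protocol defines as irrigation and control

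*Protocol article*

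**What the plan says.** All the relevant text is in the Randomization section of the protocol article.

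- **Allocation.** Participants "will be randomly divided into groups A and B by randomization", with equal probability.
- **Meaning of the labels.** The first arm is defined thus: "Group A. This is a group of patients who will be subjected to transanal irrigation (experimental". The second follows: "Group B. This is a group of patients who will receive only the best currently in use maintenance treatment (control".
- **Aim.** It is stated that "the staff performing the statistical analysis will not know which group the subject belongs to".
- **Who is masked.** "Only the data analysts will be blinded to the patients groups".
- **How.** The analysts "will get only data with names of Groups A and B, without any notification, of which group is which".
- **Coding.** The only replacement of information described is that "the name and surname of the subject will be replaced by a special code, restricting the identity of the subject".

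**The concern.** Masking an analyst by label works only if the label carries no meaning for the analyst. Here the labels to be handed over have the same names as the randomized groups, and the protocol says in print what each name stands for. Withholding the key has little effect when the key is in the document that any analyst of the trial would be expected to read.

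The stake is selective analysis. No one other than the analysts is said to be masked, and patients will know whether they irrigate each day. Masked analysis is thus the only blinding safeguard the article offers. It has real work to do, because some choices that shape the primary result are not settled in the article. If those choices were made by someone who could tell the arms apart, they could be steered, even unintentionally, by which option favours irrigation. A report that relied on the article's wording could then describe the analysis as blinded without a procedure that ensures it.

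**Working it through.** No arithmetic underlies the main point. It rests on setting the statements side by side and then counting what the text leaves open.

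**Step 1: compare the labels.**

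| Item in the Randomization section | Label used |
|---|---|
| Groups to which patients are randomized | A and B |
| Irrigation, experimental | A |
| Supportive care, control | B |
| Arm names in the analysts' data | A and B |

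The second and third rows decode the fourth. Nothing in the section says that A and B in the data file mean something different from A and B in the arm definitions.

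**Step 2: look for a second code.** The coding described replaces the patient's name. That hides who the patient is and leaves the arm label unchanged. The Data collection and Data management sections deal with depersonalization, passwords and access by site, and mention no recoding of the arm. In Appendix 1, the SPIRIT checklist items on blinding (17a and 17b) give only a page number.

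**Step 3: see what an analyst who knew the arms could choose.**

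- *Visit.* Study design and Assessments have the questionnaires repeated every 3 months for 1 year, which is 12 / 3 = 4 follow-up visits. No primary visit is named.
- *Summary of the outcome.* Sample size makes the LARS score, compared by unpaired t test, the primary endpoint. Objectives and Outcome measures instead frame the comparison as the percentage of patients in each arm whose symptoms are reduced. That gives 2 summaries.
- *Count.* 4 visits × 2 summaries = 8 combinations of visit and summary that the article could be read to support.

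This count shows how much room the text leaves. It does not estimate bias.

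**Step 4: check the timing.** Sample size plans 40 patients, and Trial status reports 24 included by January 2024, so 40 − 24 = 16 were still to come. With one year of follow-up each, and if the target of 40 is kept, the last patient could not finish before January 2025. At that revision there was time to correct the procedure before the final analysis.

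**The case against.** **The labels may be scrambled in practice.** The section states twice that analysts are not to know the groups, and A and B in their file could be generic labels unrelated to the arm definitions. The text does not exclude this. It does not say it either, and on its plain wording the file carries the protocol's own group names. This objection limits the claim to the procedure as written.

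**The article is condensed.** Who holds the key and when it is released are commonly left to a full protocol, a data-management plan or an SAP. That is fair, and the absence of those details is not the point. The point is that the mechanism the article does state reuses labels that the article itself decodes.

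**The primary analysis is specified.** This is partly right. A reader might infer that the primary endpoint is wholly open, but Sample size names the LARS score and the unpaired t test, and Statistical analysis names intention to treat. What remains open in this text is the visit and the tension between score and proportion. An SAP may settle both, and fixing them in advance would protect against selective analysis more directly than relabelling.

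**The benefit is modest.** This stands. Neutral labels can sometimes be guessed once a direction of effect appears, and analyst masking does not touch the bias from self-reported outcomes in unblinded patients.

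**Two stronger readings.** A reader might infer that the blinding is void and that every row of the file is unmasked from the first day. That assumes both that the analyst applies the published definitions and that the labels are never scrambled, and the article establishes neither. A reader might also infer that the electronic journal of irrigation inconveniences, described under Management and safety, reveals the arm. The article does not say that the journal enters the analysts' file, and several of the listed complaints, such as nausea and bloating, are not unique to irrigation.

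**Conclusion.** The point holds for the procedure as written. The protocol claims that analysts are blinded and describes a mechanism that its own arm definitions decode. This is a stated property that the stated method does not deliver, and it should be corrected.

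Its size is that of a missing safeguard. There is no evidence of bias and no figure to attach to it. It matters mainly where the article leaves the primary visit and the choice between mean score and proportion improved unsettled, and it would matter less if an SAP fixed both before anyone saw outcome data by arm. The conclusion rests on two assumptions: that the labels in the analysts' file are the randomization labels, as the wording implies, and that analysts have access to the protocol, which is published.

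**What to change.** - Have someone outside the analysis recode the arms to neutral labels unrelated to A and B, for example X and Y, by a random draw.
- Hold the key outside the analysis until the data are locked and the primary analysis script is final, and say so in the protocol.
- As a precaution, keep any field that would reveal the arm out of the analysts' file until then.
- If this is not to be done, delete the statement that the analysts are blinded.

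The cost is a small data-management task and a sentence or two of protocol text, with no effect on patients, recruitment or sample size. The change does not address bias from self-reported outcomes in unblinded patients, and it should not be presented as doing so.

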### Interventions

During the study, transanal irrigations will be used, which are considered safe procedures that do not pose additional risks to the patient.

#### Transanal irrigation

Transanal irrigation will be applied to patients who will enter the experimental group. The patient lies on the left or right side depending on the main hand with the knees bent. With the main hand, the TAI tip (cone catheter) lubricated with a lubricant is carefully introduced. The TAI bag (Coloplast Peristeen Transanal Irrigation System) is filled with warm water—it can be boiled or just from the tap. The contents of the TAI bag are slowly administered through the anus—the cone catheter is inserted [the starting volume is 500 ml of warm (around body temperature) water and it can be increased up to 1 L eventually over a 3- to 4-week period]. The duration of the TAI is about 15–20 min. Afterward, the subject goes to defecate until the bowel is empty. This action should be repeated daily.

The patients will be instructed by the treating physician and will be contacted within 3–4 weeks on the course of the procedure.

In case of bleeding or abdominal pain, patients were instructed to contact the team member at any time. For all other questions regarding TAI, the instructor could be contacted during office hours. All the adverse events and complications will be assessed weekly. In case of the high number of complications, the study will be ended.

#### Best supportive care

The control group will receive best supportive care: diet modification (low-fiber diet and personal recommendations were given), medications (bulk-forming agents and loperamide), and, if needed, diapers. All patients were instructed regarding the pelvic floor muscle training (Kegel exercise).

No patients received biofeedback therapy or any other interventions such as sacral nerve stimulation or percutaneous tibial nerve stimulation.

All the team members will be provided with the video teaching material and instructions for the procedures to be performed for both groups.

### Assessments

Data collection will take place during the patient visit. Demographic and clinical examination data will be collected from the medical documentation at the research center. During the visit, the patient's complaints after the operation (defecation, deterioration of quality of life) will be recorded, and LARS, Wexner scale, and quality of life questionnaires will be filled during the visit. Questionnaires and scales will be filled again during the visit every 3 months for 1 year. Other tests that will be performed during the visit will be long-term follow-up tests, an integral part of the treatment, not related to the clinical trial.

At the second stage, a longer follow-up will be planned—for more than 2 years after the end of treatment.

### Sample size

A sample size of 40 is planned (an improvement of 5 points on the LARS scale):
•20 transanal irrigation group (experimental) and•20 best supportive care group (control).To demonstrate a 5-point difference (with 80% certainty) between the intervention group and the control group, 34 patients were required to participate in the study (17 in each study arm). Taking into account a drop off of 20%, at least 20 patients per group will be needed. The primary endpoint was LARS score analyzed by unpaired *t* test.

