## Introduction

Neoadjuvant treatment with low anterior resection and the formation of anastomosis provides excellent oncological results and is currently the gold standard of rectal cancer treatment (1). Preoperative chemoradiotherapy, vascular dissection, and surgical removal of the rectum and mesorectum cause significant colorectal motility impairment. This results in a variety of symptoms (multiple bowel movements, recurrent urge episodes, hoarding, urinary, fecal incontinence, etc.) that are associated with severe impairment of quality of life. These complaints are summarized as low anterior resection syndrome (LARS) (2). Moreover, surgery may lead to increased morbidity, prolonged hospital stay, readmission, sepsis, and death (3, 4).

Our previous studies showed the prevalence of LARS following rectal surgery in Lithuania reaches up to 75% (5). More importantly, it is a long-term effect—50% of patients have these symptoms 5 or more years after the surgery (6).

Transanal irrigation (enema) (TAI) is a promising treatment modality for LARS patients with increasing prospective data from published studies (7). Only a few clinical trials have been published in the literature where the benefit of transanal irrigations in the treatment of LARS has been investigated (8–10). In 2018, a study conducted in Italy (8), with 27 patients, evaluated transanal irrigation as a potentially beneficial treatment modality in the treatment of LARS. It was shown that the use of TAI demonstrates notable efficacy in treating LARS and resulted in improved continence and quality of life. However, this study included patients with chronic LARS as well as patients with early symptoms following the surgery. Some patients’ symptoms may improve over the time following the operation, while others can suffer from colonic dysfunction and nerve damage, which are strongly related to the main symptoms of LARS, but do not seem to be influenced by time (8). Similar studies were conducted in Germany (2018 and 2023) (9, 10), which have also shown the benefit of transanal irrigation in controlling LARS, but due to time constraints, some patients refused this method. While patients treated by TAI showed significant improvements in bowel movements, a notable portion decided to stop the treatment and relied on supportive therapy only (9).

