Despite these data, the use of TAI remains a matter of debate. In addition, there are only few randomized clinical trials so far comparing TAI with best supportive care (8, 9, 11, 12). Main limitations of this study are that a significant amount of patients (six patients, reduction of 27.27%) dropped out of the intervention (TAI) group (9), the small numbers, and the short follow-up period (8, 11, 12).

Thus far, there are no randomized clinical trials confirming or denying the hypothesis regarding the most effective treatment for LARS. Treatment recommendations for LARS have been published in 2021 (13). Here, authors propose to initiate the treatment with best supportive treatment. If it fails, transanal irrigations are started. Moreover, if this fails, invasive procedures are recommended (such as sacral nerve modulation or stoma). Some authors recommend the perineal stoma as an alternative stoma formation site in patients were sphincter preservation is not possible (14). However, data on the risk of LARS in this subgroup of patients is still lacking.

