### Statistical analysis

For statistical analysis, we will use the intention to treat principle.

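### The 20% drop-off is handled only as lost numbers, although intention to treat keeps patients who stop irrigation; either way, 20 per arm need not give 80% power

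*Protocol article*

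**What the plan says.** Under Sample size, the protocol article states: "To demonstrate a 5-point difference (with 80% certainty) between the intervention group and the control group, 34 patients were required", that is, 17 per arm. It then adds "Taking into account a drop off of 20%, at least 20 patients per group will be needed". The same paragraph names the test: "The primary endpoint was LARS score analyzed by unpaired" *t* test. It gives no SD, alpha or sidedness, and does not say whether drop-off means a missing score, stopping the allocated treatment, or both.

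Under Statistical analysis the article fixes the population: "For statistical analysis, we will use the intention to treat principle".

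The Introduction describes earlier experience with irrigation. As a limitation of an earlier trial it reports that "six patients, reduction of 27.27%) dropped out of the intervention (TAI) group". Of patients treated with irrigation in the same cited study it says that "a notable portion decided to stop the treatment and relied on supportive therapy only". Supportive care is the control treatment here (Best supportive care).

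**The concern.** Two different events can hide under drop-off. A patient with no LARS score leaves the analysis, and recruiting more patients makes up for that. A patient who stops irrigation but is still scored remains in the irrigation arm under intention to treat. If that patient then does no better than on supportive care, the difference between arms shrinks, and adding patients in proportion to the drop-off does not bring it back. The sample-size paragraph makes only the first kind of allowance, while the Introduction shows that the second kind is foreseeable.

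What is at stake is how a non-significant result is read. If power is nearer two in three than four in five, failing to detect a 5-point effect of irrigation is a likely outcome, and the report would still claim 80%. An undefined drop-off also leaves room to set aside patients who stop, which would break the randomised comparison.

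**Working it through.** **Inputs from the article:** difference 5 points; power 80%; 17 per arm before and 20 per arm after the allowance; drop-off 20%; equal allocation; unpaired t test; intention to treat; 27.27% drop-out from irrigation in an earlier trial.

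**Assumptions:** two-sided 5%; SD back-solved, because none is printed. The figure of 17 therefore cannot be checked forwards; it is reproduced by construction.

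**Step 1, implied SD.** Power is the probability that a noncentral t with 2n − 2 degrees of freedom and noncentrality Δ / (σ√(2/n)) exceeds the critical value. Setting n = 17, Δ = 5 and power 80% gives Δ/σ = 0.991, so σ = 5/0.991 = 5.05.

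**Step 2, loss of scores only.** With all 20 per arm scored and Δ = 5, power is 86.3%. With 20% of 20 missing, 16 per arm remain and power is 77.4%. Keeping 17 after a 20% loss needs 17/0.8 = 21.25, so 22 per arm; 20 per arm covers a loss of 3 in 20, or 15%.

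**Step 3, stopping with scores kept.** Let a fraction q of the irrigation arm stop and keep a fraction r of the benefit. If 5 points is the full-adherence effect, the intention-to-treat difference is 5 × [1 − q(1 − r)]. The mixture also widens the irrigation arm, so the pooled SD becomes √(σ² + q(1 − q)[5(1 − r)]²/2). For q = 0.20 and r = 0 this is √(5.045² + 0.16 × 25/2) = 5.24.

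For 20 scored per arm and q = 0.20:

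| Benefit kept by stoppers | Difference | Power, SD unchanged | Power, wider SD |
|---|---|---|---|
| none | 4.00 | 68.6% | 65.3% |
| a quarter | 4.25 | 73.8% | 71.9% |
| half | 4.50 | 78.5% | 77.7% |
| 60% | 4.60 | 80.2% | 79.7% |
| three quarters | 4.75 | 82.7% | 82.5% |

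Simulation of the first row (200,000 trials) gives 65.1% with a random number of stoppers and 65.6% with exactly four.

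**Step 4, both events together.** With 16 scored per arm, 20% of the scored irrigation patients stopping and no retained benefit, power is 58.3% (SD unchanged) or 55.2% (wider SD).

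**Step 5, sensitivity.**
- At 27.27% stopping with no retained benefit and 20 scored per arm, the difference is 5 × 0.7273 = 3.64 and power is 56–60%.
- A one-sided 5% test implies an SD of 5.74. Power is then 85.6% with full adherence, 77.8% with 16 per arm, and 68–70% with 20% stopping and nothing retained.
- The normal approximation (SD 5.20) gives 86.0%, 77.6% and 65–68% for the same three cases.

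**Step 6, if 5 points is already the net difference.** Step 3 then does not apply. With stoppers retaining nothing, the effect in continuing patients would have to be 5/0.8 = 6.25 points at 20% stopping. Power is 86% if all are scored and 77% if 20% are not.

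**The case against.** The strongest reply is that the article never says drop-off means stopping irrigation. It applies the 20% to both arms alike, and control patients have no irrigation to stop, so missing scores is the more natural reading. The Introduction describes other studies and does not define the term. This stands: the 20% cannot be called the plan's own stopping rate. But on this reading 20 per arm gives about 77%, and stopping is not allowed for unless 5 points already includes it.

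A second reply is that the powered difference is between the two groups. Read with the intention-to-treat statement, 5 points may already be the net randomised difference. That also stands as a possible reading; the article neither says it nor rules it out.

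Third, stoppers may keep some benefit. The Discussion gives two mechanisms: an emptied bowel, which depends on continuing, and a bowel trained to a regular time, which might persist. Retention of about 60% brings power back to 80% at 20% stopping.

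Fourth, a condensed article may leave adherence assumptions to the full protocol. That lowers the weight of the point. The power statement, the allowance and the analysis population are all printed, however, and as printed they do not settle what the 80% refers to.

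**Conclusion.** The point holds as a mismatch to be cleared up, with a size that depends on the reading. If 20% per arm have no score, 20 per arm gives about 77%. If 20% of the irrigation arm stop but are scored, and 5 points is the full-adherence effect, power is about 65–69% with no retained benefit, 72–74% with a quarter and 78% with half. If both happen and nothing is retained, it is about 55–58%. All of these rest on an assumed two-sided 5% test and a back-solved SD of 5.05.

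A reader might infer more: that the 80% holds only if patients who stop are taken out of the analysis, or that the trial simply has 65–72% power. The documents support neither. Taking out 20% leaves 16 per arm and 77%, not 80%. Stated power is also met if all are scored and either 5 points is the net difference or stoppers keep about 60% or more of the benefit.

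**What to change.** Keep 40 patients and rewrite the sample-size paragraph so that it:

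- says whether the 20% means missing scores, stopping irrigation, or both, with a separate rate for each if both;
- says whether 5 points is the intention-to-treat difference after expected stopping (and, if so, gives the effect in continuing patients that this implies) or the effect under full adherence;
- prints the sponsor's own SD, alpha and sidedness, and restates power for the intention-to-treat comparison from them, not from the back-solved SD used here;
- applies the two allowances consistently, so that a power figure assuming all 20 per arm scored does not sit beside a 20% allowance for missing scores;
- states that patients who stop irrigation are still scored and are analysed in their randomised arm.

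This is rewording only. It needs no extra patients or visits and can still be done during recruitment (24 patients were included by January 2024, under Trial status). The downside is a less favourable stated power.

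### The drop-out allowance is miscalculated: 20 per arm less 20% leaves 16 evaluable, not the required 17, so the stated 80% power is missed by a small margin

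*Protocol article*

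**What the plan says.** All the relevant figures stand together in the Sample size section of the protocol article.

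- Target: "To demonstrate a 5-point difference (with 80% certainty) between the intervention group and the control group".
- Evaluable patients required: "34 patients were required to participate in the study (17 in each study arm").
- Allowance for loss: "Taking into account a drop off of 20%, at least 20 patients per group will be needed".
- Planned enrolment: "A sample size of 40 is planned (an improvement of 5 points on the LARS scale"), split 20 and 20.
- Test: "The primary endpoint was LARS score analyzed by unpaired" t test. The article gives no SD, alpha or sidedness.

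Three other places bear on the point. Randomization states equal allocation: "The probability of falling into one or the other group is equal". Statistical analysis states: "For statistical analysis, we will use the intention to treat principle". The Introduction reports, for an earlier trial of irrigation, that "six patients, reduction of 27.27%) dropped out of the intervention (TAI) group".

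**The concern.** A drop-out allowance has one job: after the assumed loss, the number still required must remain. Taking 20% from 20 patients leaves 16, one short of the 17 that the same section requires in each arm. The section therefore claims a power that its own enrolment does not deliver at its own drop-out rate.

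This does not turn on anything left to a fuller protocol or an analysis plan. The required number, the loss rate and the enrolled number are all printed, and they can be checked against each other without knowing the SD or alpha. What is at stake is the accuracy of the sample size justification. The validity of the test and the direction of any estimate are not affected.

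**Working it through.** **Inputs** (Sample size section unless noted): required evaluable n = 17 per arm, 34 in total; assumed loss d = 20%; planned n = 20 per arm, 40 in total; difference 5 points; power 80%; unpaired t test; 1:1 allocation (Randomization section).

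**1. Trying to reproduce 20 per arm.** The enrolment that keeps n evaluable patients after loss d is n/(1 − d).

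- Per arm: 17/(1 − 0.20) = 21.25, so 22 per arm, 44 in total.
- Rounding only the total: 34/0.80 = 42.5, so 43.
- The common but incorrect shortcut n × (1 + d): 17 × 1.2 = 20.4 per arm, 34 × 1.2 = 40.8 in total. Rounded up, these are 21 and 41.

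The plan's 20 and 40 appear only if the shortcut is used and then rounded down. The documents do not say how the figure was obtained.

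**2. What 20 per arm delivers.**

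- At 20% loss: 20 × 0.80 = 16 per arm, 32 in total, against 17 and 34 required.
- Largest loss that still leaves 17: 1 − 17/20 = 15%.

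**3. What the shortfall costs in power.** This step needs an assumption, because SD and alpha are not printed. I assume a two-sided alpha of 0.05 and use the exact (noncentral t) power of the two-sample t test.

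- 17 per arm reaches 80% power for 5 points at a standardised difference of 0.991, so the largest SD is 5/0.991 = 5.05.
- 16 per arm would already reach 80% at a standardised difference of 1.024, so the SD must exceed 5/1.024 = 4.88, or else 16 would have been the required number.
- Hence a requirement of 17 per arm implies an SD between about 4.88 and 5.05.

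| SD | Power, 17 per arm | Power, 16 per arm |
|---|---|---|
| just above 4.88 | about 82% | just under 80% |
| 5.0 | 80.7% | 78.1% |
| 5.045 | 80.0% | 77.4% |

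The shortfall from the claimed 80% is therefore between almost nothing and 2.6 percentage points. At the upper SD, the difference detectable with 80% power rises from 5.0 to 1.024 × 5.045 = 5.2 points.

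**4. Sensitivity case only.** If the 27.27% reported in the Introduction were a loss of LARS outcomes in the irrigation arm, 20 × (1 − 0.2727) = 14.5, so 14 or 15 would remain there. With 16 in the control arm and the upper SD of 5.045, power would be 74.3% (14 against 16) or 76.0% (15 against 16). The condition matters and is discussed under the objection.

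**The case against.** The strongest reply is that the error is too small to matter: one evaluable patient per arm, at most 2.6 points of power, in a study whose abstract calls it hypothesis-generating. That is right about size, and it argues against treating this as a serious design flaw. It does not make the sentence correct. Nor does the wording that at least 20 are needed, because the same section plans exactly 40.

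A reader might infer three stronger things. The documents do not support them.

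- **That irrigation-arm drop-out of about 27% shows 20% to be wrong.** In describing one of the same earlier studies, the Introduction says that a notable share of patients stopped irrigation and went on with supportive therapy alone. That reads as stopping treatment, which is not the same as being lost to follow-up. Under intention to treat, patients who stop irrigation but still complete the LARS questionnaire stay in the analysis; the cost is then a diluted effect, with no loss of numbers. The article gives no control-arm rate for that trial, and whether the six patients lacked outcomes cannot be seen from it. Choosing 20% is a planning judgement and no arithmetic error.
- **That the true SD is much larger and power collapses.** Nothing in the article suggests an SD of 6 to 8, and such a range has no link to the drop-out error.
- **That the absent SD and alpha are themselves a fault.** An article commonly leaves these to the full protocol or analysis plan. They limit only how precisely the power loss can be stated.

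**Conclusion.** The drop-out inflation is wrong as written. With 17 evaluable patients required per arm and 20% loss, enrolment should be 22 per arm (44 in total). The planned 20 per arm leaves 16 and covers 15% loss. This part rests on the article's figures alone and needs no assumption.

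The effect is modest: power of about 77% to just under 80% in place of the stated 80%, and about 78% at an SD of 5.0. These power figures rest on an assumed two-sided alpha of 0.05 and on an SD back-calculated from the stated 17 per arm. The 27.27% figure adds only a conditional sensitivity case, leaving 14 or 15 in the irrigation arm if those who stop irrigation also provide no LARS score.

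**What to change.** Correct the one sentence in the Sample size section. Enrolment can stay at 40, with either of these statements:

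- 20 per arm allows for 15% drop-out (20 × 0.85 = 17); or
- at 20% drop-out 16 per arm remain, with power slightly below 80% for a 5-point difference. The investigators should take the exact figure from the SD and alpha that they used; about 78% would apply at an SD of 5.0 with a two-sided alpha of 0.05.

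If the claim of 80% power after 20% loss is to stand as written, the matching number is 44. The 27.27% figure may be added as a sensitivity case, provided the text says that it reduces the analysed number only if patients who stop irrigation also lack LARS outcomes.

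Keeping 40 costs one reworded sentence and a slightly less favourable stated figure. Moving to 44 costs four more patients.
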